## Abstract

**Background:**

Whilst laterally wedged insoles, worn inside the shoes, are advocated as a simple, inexpensive, non-toxic self-administered intervention for knee osteoarthritis (OA), there is currently limited evidence to support their use. The aim of this randomised, double-blind controlled trial is to determine whether laterally wedges insoles lead to greater improvements in knee pain, physical function and health-related quality of life, and slower structural disease progression as well as being more cost-effective, than control flat insoles in people with medial knee OA.

**Methods/Design:**

Two hundred participants with painful radiographic medial knee OA and varus malalignment will be recruited from the community and randomly allocated to lateral wedge or control insole groups using concealed allocation. Participants will be blinded as to which insole is considered therapeutic. Blinded follow up assessment will be conducted at 12 months after randomisation. The outcome measures are valid and reliable measures recommended for OA clinical trials. Questionnaires will assess changes in pain, physical function and health-related quality-of-life. Magnetic resonance imaging will measure changes in tibial cartilage volume. To evaluate cost-effectiveness, participants will record the use of all health-related treatments in a log-book returned to the assessor on a monthly basis. To test the effect of the intervention using an intention-to-treat analysis, linear regression modelling will be applied adjusting for baseline outcome values and other demographic characteristics.

**Discussion:**

Results from this trial will contribute to the evidence regarding the effectiveness of laterally wedged insoles for the management of medial knee OA.

**Trial registration:**

ACTR12605000503628; NCT00415259.

## Background

Osteoarthritis (OA) is a chronic, localised joint disease affecting approximately one-third of adults, with the disease prevalence increasing with advancing age [1]. The economic impact of knee OA is also a large and growing problem for health care systems. In Australia, the estimated financial costs of OA and other arthritic diseases in 2000 totalled almost 9 billion dollars [2]. Demographic predictions indicate that people aged over 65 years will comprise more than 20% of the population by 2040 [3], thus knee OA will only become more prevalent.

The knee is the most common lower limb site for OA, with the disease affecting the tibiofemoral and patellofemoral joints either in isolation or combination. The medial tibiofemoral compartment is the most commonly affected (medial 67% versus lateral 16% [4]). Patients with knee OA frequently report symptoms of knee pain and difficulty with activities of daily living, such as walking, stair-climbing and housekeeping [5]. Ultimately, pain and disability associated with the disease lead to a loss of functional independence and a profound reduction in quality-of-life.

Management strategies for knee OA may be regarded as *primary prevention *(reduction of risk factors to reduce disease incidence); *secondary prevention *(interventions to slow/prevent progression to serious disease) or; *tertiary prevention *(treatment of pain and disability) [6]. To date, most knee OA research has focussed on tertiary management strategies, primarily drug therapies. Although effective, drug therapies have side effects and are expensive [7]. Accordingly, recent knee OA clinical guidelines reinforce the importance of non-pharmacological strategies in the management of the condition [8,9] yet there is an absence of high quality evidence to support the use of such therapies [8]. Thus there is a clear need for future clinical trials to evaluate specific non-pharmacological therapies in order to better guide clinical decision-making.

Given that there is currently no cure for knee OA and the only established treatment for end-stage OA is costly joint replacement, slowing of structural disease progression is essential to help reduce the personal and societal burden of knee OA. Traditionally, disease progression has been assessed by measuring loss of joint space over time from serial x-rays. There is now increasing use of magnetic resonance imaging to measure knee cartilage volume as it has proved to be a valid and reproducible technique that is more sensitive to change than x-rays [10]. Given the absence of a sufficiently sensitive measure of structural change until recently, this has meant that few interventions have been tested as to their effect on disease progression.

Increased load across the joint is important in the pathogenesis of knee OA. Interventions that alter knee load may reduce symptoms and slow disease progression in patients with knee OA. Direct measurement of knee joint loads is not feasible because of the invasive nature of this in vivo method. However, gait analysis can calculate external joint-loading moments that are directly related to internal joint loads. The external knee adduction moment determines load distribution across the medial and lateral tibial plateaus, with force across the medial compartment almost 2.5 times that of the lateral [11]. This may explain the much higher prevalence of medial compared with lateral tibiofemoral joint OA.

The magnitude of the adduction moment is partly determined by the mechanical alignment of the knee. In medial knee OA, mechanical alignment becomes varus as the medial joint space narrows. Varus malalignment causes the ground reaction force vector to pass more medially to the knee joint centre, resulting in a higher knee adduction moment. Cross-sectional studies demonstrate that patients with knee OA have a higher knee adduction moment during walking when compared to healthy age-matched controls [12,13].

Recent research has found that a higher adduction moment is associated with more severe knee pain [14] and greater radiographic disease severity [15]. Severity of knee malalignment is also significantly associated with knee pain severity and physical function [16]. Longitudinal studies have demonstrated that as little as a one-unit increase in the adduction moment is associated with up to a 6.5-fold increase in the risk of disease progression [14,17]. Similarly, knee joint varus malalignment is also correlated with disease progression [16,18,19]. Given the importance of the knee adduction moment and joint alignment with regard to both symptom severity and disease progression in knee OA, conservative strategies to alter these biomechanical factors constitute a logical rehabilitative approach.

In 1987, Sasaki and Yasuda [20,21] first reported the potential of a laterally wedged insole in the shoe to treat medial knee OA. They demonstrated that the insole statically aligned the knee in a more upright position by shifting the calcaneus into a valgus position relative to the tibia. The authors concluded that such an alteration helped reduce excessive loading of the medial joint surface, leading to mitigation of knee pain. Biomechanical studies have since evaluated the effects of laterally wedged insoles on knee alignment and medial compartment loading. Ogata et al [22] demonstrated that lateral thrust of the knee (which forces the knee into varus alignment) was reduced with lateral wedges in people with normal and osteoarthritic knees. Similar results have been reported by more recent studies [23-25], with Kerrigan et al [24] demonstrating that a 5° laterally wedged insole significantly reduces the knee adduction moment by 6% in medial knee OA. Finally, Giffin et al [26] observed a significant varus to valgus shift in knee alignment on static radiographs with a lateral heel wedge although this has not been a consistent finding [27]. Thus there is evidence that lateral wedges can reduce varus malalignment and the adduction moment, two key biomechanical features that are associated with knee OA symptoms and disease progression.

However, despite their biomechanical effects, few randomised controlled trials have evaluated their clinical efficacy [28-30]. In 156 patients with medial knee OA, no significant effect of laterally wedged insoles on symptoms over 2 years was demonstrated, as compared to control insoles [28]. However, a significant reduction in non-steroidal anti-inflammatory drug intake and greater compliance was observed with laterally wedged insoles, leading the authors to conclude that the results favoured a beneficial effect of the intervention. A recent double-blind, randomized, crossover trial in 90 patients found no effect of 6 weeks of lateral wedge use on pain or [30]. The samples selected for these studies may partly explain the non-significant effect of laterally wedged insoles. Whilst patients demonstrated medial knee OA, selection criteria did not consider knee joint alignment. Significant effects are more likely in participants with evidence of varus malalignment, rather than in a diverse cohort where alignment is likely to range from valgus (in which lateral wedges could be detrimental) to neutral to varus.

As previously stated, it is also important to evaluate the effect of treatment on disease progression. Only one clinical trial has investigated the effect of lateral wedges on knee OA progression [29]. Using annual x-rays for two years, this study failed to show that lateral wedges slowed joint space narrowing over time compared to control insoles. This non-significant finding may relate to the use of relatively insensitive x-rays as a measure of disease progression, as well as to an inappropriate patient group and the use of a short rather than full length wedge. Given the paucity of data attesting to the structural effects of lateral wedges over time, further research is necessary using more sensitive methods of measuring disease progression such as magnetic resonance imaging. Furthermore, no study to date has evaluated the cost-effectiveness of lateral wedges.

The aim of this trial is to determine whether wearing lateral wedge insoles for 12 months improves pain, physical function and health-related quality of life, slows structural disease progression and is more cost-effective than control flat insoles in individuals with medial knee joint OA and varus malalignment.

## Methods/Design

### Design

This will be a double-blind randomised controlled trial (Figure 1). Potential participants will undergo telephone screening followed by clinical examination by a physiotherapist or medical practitioner and a podiatrist to ensure they fulfil selection criteria. A screening x-ray will be performed to assess knee joint alignment and disease severity. Eligible participants will then be stratified by disease severity (Kellgren and Lawrence grade 2 and 3 [31] and randomly allocated in permuted blocks of 6 to 12 to lateral wedge or control flat insoles groups. The randomisation sequence will be generated *a priori *using the random number function in Excel by an independent investigator not directly involved in assessment of participants. Allocation will be sealed in opaque and consecutively numbered envelopes held in a central location. These will be opened in sequence by a person not involved in the study after recruitment and baseline testing of participants.

**Figure 1 F1:**
[figure not shown]
Trial protocol.

### Participants

Two hundred men and women aged over 50 years will be recruited from the community via advertisements in local clubs, libraries, and the print and radio media in metropolitan Melbourne, Australia. Eligibility will be confirmed by radiographic and clinical examination. People with tibiofemoral joint OA fulfilling American College of Rheumatology classification criteria [32] and reporting average knee pain on walking >3 on an 11-point scale will be included. Other inclusion criteria will be: (i) knee alignment ≤185° on a standardised semiflexed standing posteroanterior knee x-ray (which corresponds to a mechanical axis of ≤180° on a full leg xray indicating varus malalignment) [33]; (ii) predominance of pain/tenderness over the medial region of the knee and; (iii) medial radiographic OA defined as at least Grade 1 medial joint space narrowing or Grade 1 medial tibial or femoral osteophytes [34].

The exclusion criteria will include: (i) questionable or advanced radiographic knee OA (Kellgren and Lawrence stages 1 and 4 [31]); (ii) predominant patellofemoral joint symptoms based on clinical examination; (iii) knee surgery or intra-articular corticosteroid injection within 6 months; (iv) current or past (within 4 weeks) oral corticosteroid use; (v) systemic arthritic conditions; (vi) history of tibiofemoral/patellofemoral joint replacement or tibial osteotomy; (vii) any other muscular, joint or neurological condition affecting lower limb function; (viii) ankle/foot pathology or pain that precludes the use of insoles; (ix) use of foot orthotics within past 6 months; (x) regular use of footwear that does not accommodate an insole; (xi) contraindications to magnetic resonance imaging (eg. metal implant, cochlear implant, claustrophobia, pacemaker); (xii) planning to commence exercise or other treatment for knee OA in the next 12 months; (xiii) regular use of a gait aid and; (xiv) non-English speaking.

Ethical approval has been obtained from the University of Melbourne Human Research Ethics Committee (HREC No. 050031) and from the Department of Human Services Victoria, Radiation Safety Committee. All participants will provide written informed consent.

### Interventions

Participants will be informed that we are testing two different types of shoe insoles and will be blinded as to the types of insoles or their perceived clinical effects. To become accustomed to insole use over the first two weeks, participants will commence with one hour per day thereafter increasing by one hour per day. Participants will be asked to wear the insoles full time in their shoes. Insoles will be replaced every four months.

Participants in the intervention group will be provided with two pairs of bilateral standardised laterally wedged (5°) insoles made of high density ethyl vinyl acetate (similar to a running shoe midsole) wedged along the entire lateral border of the foot (Foot Function Ltd, New Zealand). The 5° wedge has been selected because greater wedging is unlikely to be tolerated by the wearer [24] and would be difficult to accommodate within a normal shoe.

Participants in the control group will be provided with two pairs of full length bilateral standardised footshaped flat insoles made of low density ethyl vinyl acetate (Foot Function Ltd, New Zealand). This is easily compressible soft foam that will not alter foot mechanics.

### Outcome assessment

Participants will be assessed at baseline and at 12 months by an assessor blinded to group allocation. Outcome measures have been selected based on those recommended for clinical trials of knee OA [35,36]. In those with bilateral knee OA, only the most symptomatic knee will be assessed.

Age, gender, duration of knee OA symptoms, previous treatment, surgery and medication use for knee OA will be obtained by questionnaire. Radiographic disease severity will be assessed from the baseline x-ray using the Kellgren and Lawrence grading system [31]. Skyline knee x-rays performed in nonweightbearing at 20° knee flexion will also be obtained to assess severity of OA within the patellofemoral joint. X-rays will be evaluated according to osteophytes and joint space narrowing based on a 4 point scale [34].

The primary outcomes will be knee pain and knee cartilage volume (Table 1). Average knee pain in the past week will be self-assessed by an 11-point horizontal numeric rating scale with terminal descriptors of zero = no pain and 10 = worst pain possible. Such measurement has demonstrated reliability in OA [35].

**Table 1 T1:** Outcome measures

**Primary Outcomes**	**Measurement**
Average pain in the past week	11 point horizontal numeric rating scale (end descriptors of 0 = no pain and 10 = worst pain possible)
Medial tibial compartment cartilage volume	Magnetic resonance imaging

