Participants will rate their perceived change in pain and in physical function with treatment (compared to baseline) on an ordinal scale (1-much worse, 2-slightly worse, 3-no change, 4-slightly better, 5-much better). Scales of this kind are frequently used as an external criterion for comparison with changes in scores of other outcomes [47]. Measuring patient perceived improvement using a rating of change scale has been shown to be a clinically relevant and stable concept for interpreting truly meaningful improvements from the individual perspective [48].

A number of other measures will be obtained (Table 1). Participants will record compliance of and tolerance with both types of insoles in a daily log-book. They will record the number of hours per day of insole use. At the end of the 12 months, participants will also indicate their perceived compliance with the insoles using an 11 point horizontal rating scale with terminal descriptors of zero = not at all and 10 = completely as instructed. Discomfort with the insoles will be evaluated weekly in the logbook on a 5-point ordinal scale (1 = no discomfort, 2 = mild, 3 = moderate, 4 = severe, 5 = very severe discomfort) [28]. At the end of the 12 months, participants will also rate their overall level of discomfort of the insoles using an 11 point horizontal rating scale with terminal descriptors of zero = extremely comfortable and 10 = extremely uncomfortable. Other adverse effects and the use of co-intervention will be recorded in the log-book and by open-probe questioning by the assessor at trial completion. Log-books will be posted back to the assessor on a monthly basis and checked for completion.

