### Sample size calculations

Our sample size of 200 ensures adequate power for the two principal endpoints of change in pain and change in knee cartilage volume. Assuming that lateral wedges result in a mean pain reduction of 2 on our numeric rating scale (the minimum clinically important difference to be detected in OA trials [49]), that control insoles have a small placebo effect of 0.5 and that there is a SD of change of 3 (based on our previous data evaluating conservative OA interventions [50,51]), 170 participants would be required in total to give 80% power (2 sided test, alpha = 0.05). We have previously demonstrated a reduction in pain of this magnitude with knee taping [50] and physiotherapy for knee OA [51].

The other major end point is rate of knee cartilage loss. We have previously shown that the rate of tibial cartilage loss is 5.3 +/- 5.2% per year in a cohort with knee OA [52]. We categorized OA participants into tertiles: cartilage loss <3% per annum, 3–8% per annum and > 8% per annum. We found a linear increase in the risk of undergoing a knee replacement within 4 years [53]. Participants who lost cartilage at the rate of 3–8% per annum had a 2.4 fold (0.4 to 12.2) increased risk of requiring a knee replacement compared to participants who lost cartilage at the rate of <3% per annum. Those with the highest rate of loss of knee cartilage (>8% per annum) had a 7.1 fold (1.4 to 36.5) increased risk of requiring a knee replacement. These data suggest that a clinically useful outcome with lateral wedges would be to reduce the rate of knee cartilage loss to <3% per annum. With 100 subjects in each arm of the study, we will have 80% power to show a difference between a 5.3 +/- 5.2% per year rate of cartilage loss in the control group [52] and a <3% rate of cartilage loss in the intervention group (2 sided test, alpha = 0.05). This also takes into account a 20% drop-out rate.

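### Knee pain, a self-rated co-primary outcome, has one post-randomisation score at month 12; anyone not assessed then is scored as no change, although a log-book that could carry the item comes back every month

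*Protocol article*

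**What the plan says.** The Outcome assessment section fixes the schedule: "Participants will be assessed at baseline and at 12 months by an assessor blinded to group allocation". The abstract agrees: "Blinded follow up assessment will be conducted at 12 months after randomisation". The first primary outcome is simple to collect: "Average knee pain in the past week will be self-assessed by an 11-point horizontal numeric rating scale". No other time point is given for it.

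Between the two assessments participants keep a log-book. Its listed contents, taken from Table 1 and from the Outcome assessment and Economic analysis sections, are:

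- wear time: "They will record the number of hours per day of insole use";
- insole comfort, which is not knee pain: "Discomfort with the insoles will be evaluated weekly in the logbook on a 5-point ordinal scale";
- safety and other treatment: "Other adverse effects and the use of co-intervention will be recorded in the log-book";
- health-care visits, prescription and over-the-counter medication, home care and hospital stays.

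On its return the protocol says: "Log-books will be posted back to the assessor on a monthly basis and checked for completion".

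The Statistical analysis section analyses everyone randomised by intention to treat and fills a missing value with the participant's latest available score. The Sample size calculations section closes the cartilage calculation with: "This also takes into account a 20% drop-out rate".

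**The concern.** With one follow-up, the latest available pain score for a person not seen at month 12 is the baseline score. Carry-forward then gives a change of zero by rule, whatever that person's pain did. The estimate depends on how many are lost in each arm as well as on how pain responded.

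Unequal loss is plausible here. The wedge is high-density material and the control is soft foam. The Interventions section itself doubts that a steeper wedge would be tolerated, and the Background cites an earlier insole trial in which compliance differed between arms.

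Changing the analysis method alone goes only part of the way. Without carry-forward, the missing month-12 score would have to be predicted from baseline pain and indirect log-book data (wear time, discomfort, medication, adverse effects). The most informative predictor, pain itself in the months before loss, is not collected, although the means of collecting it already exists.

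**Working it through.** **Inputs from the protocol.** 200 participants, 100 per arm; mean pain reduction 2 (wedge) and 0.5 (flat), so a difference of 1.5; SD of change 3; two-sided alpha 0.05; drop-out 20% (all from Sample size calculations). Carry-forward in everyone randomised (Statistical analysis).

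**Assumptions.** Loss is unrelated to outcome within each arm. The 20% applies to pain. The unequal splits are chosen to average 20%. Power is by normal approximation for an unadjusted comparison of change; the planned model also adjusts for baseline.

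**Step 1: the plan's own figures.** Cartilage: 2 × (1.960 + 0.842)² × 5.2² / (5.3 − 3)² gives 81 per arm, and 81 / 0.8 = 102 against the stated 100. Power with 80 completers per arm is 0.799. The 20% allowance therefore reproduces for cartilage. Pain: 2 × (1.960 + 0.842)² × 3² / 1.5² gives 63 per arm, 126 in total (128 by t-test), not the stated 170. The figure 170 is what 90% power gives with no drop-out. That discrepancy is separate, errs on the safe side and has no bearing on this point.

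**Step 2: number affected.** 0.20 × 200 = 40.

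**Step 3: effect of zero change.** If a proportion d of an arm with mean change μ is set to zero:

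- mean = (1 − d) μ
- variance = (1 − d) × 9 + d (1 − d) μ²

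For d = 0.20 in both arms:

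- wedge: mean 0.8 × 2 = 1.6; variance 7.2 + 0.16 × 4 = 7.84
- control: mean 0.8 × 0.5 = 0.4; variance 7.2 + 0.16 × 0.25 = 7.24
- difference 1.6 − 0.4 = 1.2; standard error √((7.84 + 7.24) / 100) = 0.388
- power = Φ(1.2 / 0.388 − 1.96) = 0.871

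An analysis of 80 completers per arm would have power 0.885 for a difference of 1.5, so the loss of power from carry-forward is slight.

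**Step 4: range.**

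| Loss, wedge / control | Expected difference | Power |
|---|---|---|
| 10% / 10% | 1.35 | 0.912 |
| 20% / 20% | 1.20 | 0.871 |
| 30% / 30% | 1.05 | 0.816 |
| 30% / 10% | 0.7 × 2 − 0.9 × 0.5 = 0.95 | 0.681 |
| 25% / 15% | 0.75 × 2 − 0.85 × 0.5 = 1.075 | 0.788 |
| 15% / 25% | 0.85 × 2 − 0.75 × 0.5 = 1.325 | 0.929 |
| 10% / 30% | 0.9 × 2 − 0.7 × 0.5 = 1.45 | 0.965 |

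At the same overall loss of 20%, the expected estimate runs from 0.95 to 1.45 according to which arm loses more people.

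**The case against.** The strongest reply is that a single follow-up is a legitimate design. The aim is the effect of wearing insoles for 12 months, the endpoint is 12-month change, and one assessment at that time matches both. It is neither an error nor a contradiction, and the Economic analysis section states a wish to keep respondent burden low. All of that stands. The weakness lies in combining one follow-up with carry-forward, with a monthly form that omits the outcome.

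Other limits also stand:

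- The 20% is stated for cartilage, which needs a repeat MRI. Loss for a self-rated item could be lower.
- No passage supports any particular split between arms.
- If those lost really returned to their baseline pain, zero change would be right for them. The data collected could not show it.
- Monthly scores help only where loss is related to pain that was recorded. People may stop posting log-books before they leave.

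Three stronger readings are tempting and are not supported:

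- A reader might infer that anyone who stops wearing the insoles is lost to the pain analysis. Nothing says that stopping ends follow-up, and intention to treat keeps those who attend at month 12.
- A reader might infer that any missing-data method would have baseline values alone. The log-book supplies wear time, discomfort, medication, adverse effects and co-interventions. These are weaker than a pain score but usable.
- A reader might compare completers only and quote an overstated effect. One simulation, with assumed losses of about 23% (wedge) and 9% (control) driven by pain, gave a bias of 13-29% of the effect. The plan does not analyse completers only, so this is an illustration under assumptions and not the plan's bias.

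**Conclusion.** The point holds for participants who leave or miss the month-12 assessment. They have no pain score after randomisation, and the stated rule counts each as zero change. If 20% are lost equally and at random, the expected difference shrinks by a fifth, from 1.5 to 1.2, while power stays near 0.87. The main harm is therefore bias, and its size depends on how loss divides between arms: 0.95 to 1.45 across the assumed 30%/10% and 10%/30% splits. These figures rest on the plan's own means and SD, on extending the cartilage drop-out rate to pain, and on loss unrelated to outcome within arm. They show how sensitive the estimate is and do not forecast the result. This is a cheap and worthwhile improvement; it does not invalidate the design.

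**What to change.** - Add the same 11-point past-week average pain item to the log-book once a month, naming the study knee.
- Keep month-12 change as the primary pain endpoint.
- Replace carry-forward for pain with a mixed model or multiple imputation that uses the monthly scores up to the last log-book received.
- Seek the one-item month-12 rating by post or telephone from anyone who does not attend, whether or not the insoles are still worn.

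The cost is one line in a form already completed, posted and checked, with slightly more respondent burden and data entry, and a short change to the analysis text. It needs no extra visit, procedure or participant.
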